## Abstract

**Background:**

Delirium has been long considered as a major contributor to cognitive impairments and increased mortality following a critical illness. Pharmacologic and non-pharmacologic strategies are used against delirium in the intensive care unit (ICU), despite these strategies remaining controversial. Previous studies have shown the feasibility of using virtual reality within the ICU setting, and we propose to use this technology to investigate the effect of immersive virtual reality stimulation on the incidence of delirium in the ICU. Moreover, we propose to use motion sensors to determine if patient movement patterns can lead to early prediction of delirium onset.

**Methods:**

This study is conducted as a randomized clinical trial. A total of 920 critically ill patients in the ICU will participate. The control group will receive standard ICU care, whereas the intervention group will, in addition to the standard ICU care, receive relaxing 360-degree immersive virtual reality content played inside a head-mounted display with noise-cancelling headphones, three times a day. The first 100 patients, regardless of their group, will additionally have their movement patterns recorded using wearable and ambient sensors. Follow-up measurements will take place 6 months after discharge from the ICU.

**Discussion:**

Delirium is widely present within the ICU setting but lacks validated prevention and treatment strategies. By providing patients with virtual reality stimulation presented inside a head-mounted display and noise-cancelling headphones, participants may be isolated from disturbances on an ICU. It is believed that by doing so, the incidence of delirium will be decrease among these patients. Moreover, identifying movement patterns associated with delirium would allow for early detection and intervention, which may further improve long-term negative outcomes associated with delirium during critical care.

**Trial registration:**

ClinicalTrials.gov NCT04498585. Registered on August 3, 2020

## Administrative information

The order of the items has been modified to group similar items (see http://www.equator-network.org/reporting-guidelines/spirit-2013-statement-defining-standard-protocol-items-for-clinical-trials/).

## Introduction

### Background and rationale {6a}

Critically ill patients in the intensive care unit (ICU) frequently develop delirium. The prevalence of delirium in the ICU is between 35 and 80% in ventilated and non-ventilated patients [1, 2]. Delirium is defined as a disturbance in attention, awareness, and cognition with reduced ability to direct, focus, sustain, and shift attention, and reduced orientation to the environment [3, 4]. It profoundly affects both the patients and their families as it is associated with increased mortality [1, 5, 6], increased cognitive impairment [1, 5], longer duration of mechanical ventilation [1, 6, 7], unplanned extubation and catheter removal by the patient [6, 7], and longer ICU and hospital stay [1, 5–7]. Furthermore, it has been shown that the duration of delirium is associated with worse long-term cognitive impairment [8]. Delirium may occur as a hypoactive, hyperactive, or mixed form. Unfortunately, delirium often evades diagnosis as it most frequently presents with hypoactivity and somnolence [3]. Conversely, it can be more easily recognized when patients are hyperactive or agitated [3].

In prevention and treatment, pharmacological and non-pharmacological strategies are discussed [5]. Pharmacologic prevention and treatment of delirium remains controversial [5, 9, 10]. Despite this, in hyperactive patients, pharmacological measures are used in the clinical setting, with typical and atypical antipsychotics and dexmedetomidine recommended for controlling the symptoms [9]. In the Clinical Practice Guidelines for adult patients in the ICU, Devlin et al. do not recommend the use of haloperidol, atypical antipsychotics, or statins, for treating delirium except in patients experiencing distress, or showing signs of agitation or hallucinations, unrelated to the delirium [5]. All three drugs were not found to decrease delirium duration, duration of mechanical ventilation, ICU length of stay, or mortality [5]. Similarly to haloperidol, the effectiveness of dexmedetomidine in patients with delirium without agitation, or with agitation not related to being mechanically ventilated, remains unclear [5].

Despite non-pharmacological strategies also lacking clinical evidence of their efficacy, single- or multicomponent interventions, such as early mobilization, sleep improvement, and reorientation, are often used for preventing or treating delirium [5, 11]. One advantage of using multicomponent strategies, as opposed to single component approaches, proposed in the literature, is that multicomponent strategies may target more than one risk factor for delirium simultaneously [12]. In this way, there is a greater potential of having a beneficial effect, even in the absence of strict compliance.

In a pilot study, Gerber et al. [13] showed the feasibility, usability, and acceptance of virtual reality (VR) stimulation (i.e. relaxing nature videos) as a new non-pharmacological intervention to comfort patients during their stay in the ICU. Currently, head-mounted displays have been widely used therapeutically in individuals with various mental and physical disorders [14–16]. Two studies conducted by Gerber et al. [17, 18] produced evidence that VR stimulation with a head-mounted display in ICU settings is potentially beneficial for patients. More specifically, the relaxing effect produced by the VR stimulation has a high potential to reduce the incidence of delirium. Furthermore, VR-based cognitive stimulation in critically ill patients did not evoke any negative reactions and is thus safe to use in this population [13, 17, 18].

For the two main aims of this randomized clinical trial, we focus on (1) reducing the incidence of delirium by using VR stimulation and (2) analysing movement patterns in order to obtain indicators as to the occurrence of delirium.

### Objectives {7}

The primary objective of this randomized clinical trial is to analyse the effect of VR stimulation on the incidence of delirium after admission to the ICU. Participants in the control group will receive the standard ICU care, while participants in the intervention group will additionally receive VR stimulation. We hypothesize that participants receiving the VR stimulation will have a lower incidence of delirium during their stay in the ICU, compared to the control group. The secondary objectives are to evaluate differences in movement patterns and intensity between the intervention and control groups and between participants with delirium and without delirium. We expect that these differences will be related to the different types of delirium (i.e. hyperactive, hypoactive, or mixed). Additionally, it is predicted that it will be possible to detect differences in movement patterns between groups and identify patterns indicating the presence or absence of delirium. Secondary objectives also include the evaluation of the effect of VR on duration of delirium. In this case, it is hypothesized that the duration of delirium will be shorter in participants receiving the VR stimulation compared to those in the control group.

Further objectives which will be addressed include (1) evaluating the effect of VR stimulation, identified by changes in physiological parameters; (2) evaluating how easily the VR stimulation can be provided to patients by critical care professionals; (3) describing differences in cognition, health-related quality of life, and functional independence between groups, using questionnaires; and (4) evaluating if VR reduces the need for pharmacological treatment of delirium.

### Trial design {8}

This study is conducted as a randomized clinical trial with a superiority framework and a parallel group design. There are two distinct groups; the control group will receive standard ICU care, whereas the intervention group will, in addition to the standard ICU care, receive relaxing VR stimulation three times a day.

## Methods: participants, interventions, and outcomes

### Study setting {9}

The study will be conducted in the interdisciplinary adult ICU of the University Hospital of Bern, (Inselspital), a Swiss university hospital. Data will be recorded solely at this location.

### Eligibility criteria {10}

All patients in the ICU, including patients with acquired brain injury, are eligible to participate in this study. The interventions will be performed by trained ICU nurses.

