#### Exclusion criteria

Known psychotic disorders associated with delusions (e.g. schizophrenia, dementia)Recent history of major depressionAdmission for drug overdose

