### Outcomes {12}

The primary outcome is delirium incidence, measured three times a day (morning, midday, and evening) by the Intensive Care Delirium Screening Checklist (ICDSC) as part of standard assessment. With the ICDSC, delirium is determined by consciousness, inattention, disorientation, hallucination, agitation or retardation, speech and mood, sleep/wake cycle disturbance, and fluctuation [19]. A unique incidence of delirium is counted once a patient reaches a score of ≥ 4, on a scale from 0 to 8 [20]. The entire period that a patient has a score ≥ 4 is considered as a single episode, and accordingly, counts only as a single incidence. The mean incidences of delirium per group will be looked at. The incidence of delirium is considered to be clinically relevant as it is known that patients who experience delirium while in critical care have worse long-term outcomes [4]. Furthermore, due to the possible influence of sedatives and analgesics on the incidence of delirium, both sedation and pain levels will be assessed every 2 h [5]. Consciousness and sedation will be measured using the Glasgow Coma Scale [21] and the Richmond Agitation Sedation Scale [22], respectively, and pain will be measured using the Numeric Rating Scale [23] and the Behavioural Pain Observation Tool [24].

As a secondary outcome, the duration of delirium will be evaluated per 8-h periods, or as needed, while patients are in the ICU. If the participant is assessed as delirious via the ICDSC during any of the assessments during an 8-h span, the entire period will count as delirious. Duration of delirium is clinically relevant knowing that the duration of delirium is an independent predictor of mortality 6 and 12 months post-ICU admission [25, 26].

Additional secondary outcomes include the pattern and intensity of movements, before and during delirium as well as between groups, measured continuously during the ICU stay. The fact that patients in delirium have fluctuating motor performance movement patterns, differing from baseline, could be a possible marker for delirium detection [27]. Therefore, acceleration will be measured with wearable sensors such as inertial measurement units, which have been previously used successfully in the ICU [28]. The monitoring of patients’ movement patterns could provide a means of early detection of delirium, permitting early intervention by the care staff.

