## Discussion

One challenge we will face during this study is the unpredictable reaction of patients to the VR stimulation when they are in a state of delirium. As such, the feasibility of providing VR stimulation to participants when they are already in a state of delirium is unknown. This can specifically be a problem due to their increased motor activity if they are in hyperactive delirium. Furthermore, there is a risk that delirious participants will not tolerate wearing such a head-mounted display and headphones and may even try to remove the items themselves. This may become a limitation in participant recruitment, as it does occur that patients enter into a state of delirium shortly after ICU admission. The study team will continue to provide the stimulation for as many days, and as consistently as possible; however, participant safety and comfort is the priority and, therefore, this aspect of unpredictability remains.

There currently remains the open question as to what specific aspect of the VR may be responsible for the effect we see, if any. Specifically, it is not known if it is the combination of audio and visual input, or the one or the other alone that creates an effect. Alternately, it could be that using these devices allows the patient to avoid noise overstimulation by using headphones and visual overstimulation by using the headset. This remains an open question.

It should be kept in mind that a limitation of the current study is the sparse literature confirming the reliability and validity of the questionnaires listed above, specifically for use in a language other than English and for our target group of ICU patients. The reliability and validity of the measures listed earlier are largely based on English speakers across a variety of patient populations and healthy controls. Therefore, we acknowledge that these values may not hold true, and applying it to participants in a language other than English may result in bias being introduced. Regarding the validity of the ICDSC, which we use for our primary outcome, the validity for the German version has not been assessed. Because of this, we will cross-check the score of the ICDSC with the Richmond Agitation Sedation Scale score. A positive Richmond Agitation Sedation Scale score is an important indicator of delirium based on symptoms that keep patients in the ICU, and therefore, should correspond to the ICDSC score.

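### Some brain-injured participants may score 4 or more on the ICDSC from the injury and not from delirium; the unadjusted primary test absorbs this as lost power, part of which stratification can recover.

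*Protocol article*

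**What the plan says.** Eligibility criteria {10} admits all ICU patients, "including patients with acquired brain injury, are eligible to participate in this study". The listed exclusions (psychotic disorders including dementia, recent major depression, admission for overdose) do not touch this group. Among the inclusion criteria, the ability to keep the eyes open for 30 seconds is the one that bears on level of consciousness.

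Outcomes {12} says that on the ICDSC "delirium is determined by consciousness, inattention, disorientation, hallucination, agitation or retardation, speech and mood, sleep/wake cycle disturbance, and fluctuation". It continues: "A unique incidence of delirium is counted once a patient reaches a score of" 4 or more on a scale of 0 to 8. A run of such scores "is considered as a single episode, and accordingly, counts only as a single incidence". The section asks for no change from a baseline state, does not make fluctuation mandatory, and gives no rule for attributing a feature to a structural injury.

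The article does see that the outcome can be confounded, but names drugs only: "due to the possible influence of sedatives and analgesics on the incidence of delirium, both sedation and pain levels will be assessed every 2 h". The Discussion adds that "we will cross-check the score of the ICDSC with the Richmond Agitation Sedation Scale score", because the German version has not been validated.

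Randomisation is stratified by gender and age (Sequence generation {16a}). The primary comparison is a chi-square test of proportions with no covariate (Statistical methods {20a}). The additional analyses in {20b} concern movement data.

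**The concern.** Five of the eight listed features describe functions that a brain injury can disturb directly: consciousness, attention, orientation, speech and psychomotor activity. Four points make a case. A patient could therefore cross the threshold without hallucination, sleep disturbance or fluctuation, and the stated outcome would count that patient as delirious. VR would not be expected to prevent points that come from the injury.

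A comparison with the sedation scale cannot tell the two causes apart. The blinded interim look is no safeguard either, since a pooled rate does not show how much of it is injury-driven.

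At stake is the power of the single primary test. A null result would also be harder to read, because it could mean that VR does not work or that part of the outcome was not delirium. Duration of delirium could be affected as well, since a fixed deficit would keep the score at 4 or more and count as continuing delirium.

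**Working it through.** **Inputs from the article.** Delirium rates 39% (control) and 30% (intervention); 460 per arm; two-sided 0.05; stated power 80% (Sample size {14}).

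**Reproducing the plan's figure.** The standard two-proportion formula for 80% power gives a total of 874 without continuity correction and 918 with it. The stated 920 matches the corrected version, so there is almost no reserve. (The same section also states a power of 0.95. That would need 1,446 participants, or 1,490 with correction. It is a separate discrepancy.)

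Power without correction is Φ[(Δ − 1.96·s0)/s1], where s0 = √[2p̄(1−p̄)/n] and s1 = √{[pC(1−pC) + pI(1−pI)]/n}. For 39% against 30% with n = 460: (0.09 − 1.96 × 0.03134)/0.03120 = 0.915, so power is 0.820.

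**Assumptions, not in the article.** A share f of participants has acquired brain injury, and a share q of these scores 4 or more from the injury in either arm. Then k = f × q of all participants are fixed positives. Everyone else has the planned 39% or 30%. Observed rates are k + (1−k) × 0.39 and k + (1−k) × 0.30.

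| f, q | k | Observed rates | Difference | Power, plain test |
|---|---|---|---|---|
| none | 0 | 39.0% v 30.0% | 9.0 points | 0.820 |
| 10%, 30% | 3% | 40.8% v 32.1% | 8.7 points | 0.786 |
| 20%, 50% | 10% | 45.1% v 37.0% | 8.1 points | 0.705 |
| 30%, 70% | 21% | 51.8% v 44.7% | 7.1 points | 0.579 |

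This is the milder version. If the planned 39% already contains the fixed positives and the ratio 30/39 applies only to the remainder, power is 0.754, 0.563 and 0.256 at the same k.

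**What stratification recovers.** For a Mantel-Haenszel test with two equal strata of n_s per arm, T = Σ(n_s/2)Δ_s. Its null variance is V0 = Σ n_s·p̄_s(1−p̄_s)/2, and its variance under the alternative is V1 = Σ n_s[pC(1−pC) + pI(1−pI)]/4.

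Middle scenario: 92 per arm with injury (69.5% v 65.0%) and 368 per arm without (39% v 30%).
- T = 46 × 0.045 + 184 × 0.09 = 18.63; V0 = 51.71; V1 = 51.31.
- (18.63 − 1.96 × 7.191)/7.163 = 0.633, so power is 0.737.

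| k | Plain test | Stratified by injury | Injured patients left out (total N) |
|---|---|---|---|
| 3% | 0.786 | 0.792 | 0.779 (828) |
| 10% | 0.705 | 0.737 | 0.729 (736) |
| 21% | 0.579 | 0.663 | 0.672 (644) |

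The stratified column depends slightly on the variance used; with V1 throughout, the last row is 0.665. Gender and age are not modelled, because the article gives no rates by these factors.

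**The case against.** The strongest reply is that the key step is not in the document. The article names the features and cites the instrument, but does not show how items are scored or whether a stable deficit earns a point. This stands. A reader might infer that fixed deficits do reach 4; the text supports only that they may. The eyes-open criterion also removes the most obtunded patients.

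Second, the shares are assumed. The nearest figure in the article is an ICDSC specificity of 95% in ICU patients. It is not specific to brain injury, but as a 5% fixed-positive rate it gives power of 0.76. At the low end of the range, 0.79 against a planned 0.80 is negligible. Both remarks are fair.

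Third, a reader might infer that the trial is biased towards VR or that its type I error is raised. Neither follows. With randomised arms such cases should be balanced apart from chance, and they pull the difference towards zero. Admitting these patients is a deliberate choice of a broad population, not an error. Nor would a null result be beyond interpretation: disease-related data are collected, so a later analysis by diagnosis would be possible, though post hoc unless named beforehand.

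Last, it may be said that this belongs in an analysis plan that is not shown. The reply is only partly right. The article itself fixes the population, the case definition and an unadjusted test, and the stated test can be improved at almost no cost.

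**Conclusion.** The point holds as a matter of dilution. The article admits brain-injured patients, counts any total of 4 or more, and compares the arms with a plain chi-square test. Injury-driven scores can therefore enter the outcome and reduce power. The loss runs from trivial (0.79) to serious (0.58) as the assumed fixed-positive share goes from 3% to 21%, and it is larger if the planned 39% already includes such cases. The size rests wholly on assumed shares, and the mechanism on an inference from feature names. Nothing in the document supports a claim of bias in favour of VR, or that brain-injured patients as a class would be misclassified.

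**What to change.** In Statistical methods {20a}, replace the unadjusted chi-square test with a test stratified by acquired brain injury at admission (yes/no) together with the randomisation factors gender and age, for example Cochran-Mantel-Haenszel. Name in advance one sensitivity analysis: the primary comparison in participants without acquired brain injury. Eligibility and sample size need not change on this account.

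The cost is analysis wording and one further analysis. Brain-injury status should be obtainable from the disease-related data already collected, but it must be recorded as it was at admission so that nothing arising after allocation can influence it.

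There are two limits. Stratification recovers only part of the lost power and leaves the misclassified cases in the outcome. The sensitivity analysis is less precise (about 644 participants if 30% have brain injury), so it serves to interpret the primary result and not to replace it.

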#### Inclusion criteria

Aged ≥ 18 years with no upper age limitNo severe visual or auditory impairments (diplopia, low vision due to macular degeneration, retinopathy, severe hypacusis, or deafness)Estimated length of stay > 24 hCan keep eyes open for at least 30 sGerman or French speaking

#### Exclusion criteria

Known psychotic disorders associated with delusions (e.g. schizophrenia, dementia)Recent history of major depressionAdmission for drug overdose

### Who will take informed consent? {26a}

All patients who meet the inclusion criteria will be approached by a member of the study team within 24 h of ICU admission. However, since patients are often unable to give consent due to their condition and the situation of their relatives or authorized representative is often unclear at the beginning, a neutral physician may be consulted before the patient is included in the study. The neutral physician who is not involved in the study and who safeguards the participant interests provides a written authorization to enrol the patient.

If a proxy consent is not obtainable because no relatives and/or representative is identified or the representative cannot be reasonably contacted, the patient will stay in the study and their data will be used in order not to compromise the results of the study.

In the case where the patient is discharged from the ICU in a state of capacity that does not allow him/her to provide consent, a re-evaluation of their capacity to consent will only be done during the study follow-up visits or telephone follow-up calls (6 months visits). If the patient cannot provide informed consent at 6 months post-discharge, the relatives and/or representative will be asked again to provide informed consent to use the study data.

Informed consent will be obtained by a member of the study team after providing the patient, family member(s), or authorized representative with both verbal and written study information about what the study entails (e.g. its benefits, risks, design) and what the informed consent states. If the patient, family member(s), or an authorized representative agrees to participate in the study, they will be asked to sign a written consent form for their study participation. If a family member or authorized representative provides consent on the patients’ behalf, the patient will be asked directly for their consent as soon as their health condition allows. The patient will again be asked for their written informed consent 6 months post-ICU discharge to participate in a 6-month follow-up visit.

